### Data management

Each participant will be allocated a unique participant number. Data will be coded and entered into an Excel spreadsheet in de-identified form. Data will be double checked by a secondary data analyst. Data will be stored securely in a locked cabinet for 10 years, or in a password-protected secure computer file. Data will be destroyed after 10 years.

All principal investigators will be given access to the cleaned and password-protected data set.

### Quantitative data analysis

Data analyses will be performed by a biostatistician blinded to treatment allocation using intention-to-treat and per-protocol analyses. The per-protocol analysis group refers to those participants who completed the treatment as originally allocated. We have defined this as participants who undergo at least six of the maximum nine total number of EMDR treatment sessions or who fulfill the criteria for early completion.

Baseline differences in demographic and clinical characteristics between the EMDR and control group will be analyzed using chi-squared tests, *t* tests, and analysis of variance. Descriptive statistics will provide data summaries. Continuous variables will be analyzed on an intention-to-treat basis with linear mixed models. For the PSYRATS data, which is usually not normally distributed because of a disproportionate number of zero scores, differences will be analyzed using the Wilcoxon signed-rank test and the Mann–Whitney *U* test.

Baseline scores will be included as covariates, time as a categorical variable, and treatment condition as a fixed effect. The intercept will be treated as a random effect. Dichotomous outcomes will be analyzed with logistic generalized estimating equation analyses with exchangeable correlation structure.

Effects will be calculated for post treatment and 6-month follow-up using interaction effects. Analyses of completers and intent-to-treat analyses with the last observation carried forward (with missing data on loss of diagnosis conservatively replaced with a negative value, i.e., no loss of diagnosis) will be performed to test the robustness of the findings.

The number needed to treat will be calculated to determine the number of participants who needed to be treated to make one more patient lose the PTSD diagnosis or achieve full remission compared with the control condition.

All tests will be two-sided and *p* < 0.05 will be considered statistically significant. We will use multiple imputations for missing data.

A biostatistician is part of the research team.

For the qualitative data, thematic analysis will be undertaken using NVivo software (QSR International). Two researchers will independently read and code the transcripts, the codes will be examined, and by an iterative process the codes will be condensed into groups that capture similar themes, each with a number of subthemes. These themes and subthemes will be considered by the research team, to validate the plausibility of the themes. To achieve saturation of the themes, the researchers will move back and forth between data collection and analysis, ensuring the fit between the data, and the conceptual work of analysis and interpretation. Work completed early in the study will inform subsequent recruitment, data collection, and analysis.

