**Methods:**

This is a single-blind, randomized controlled trial comparing EMDR therapy to the waiting list (routine care). Adult forensic mental health service users (*n* = 46) with SMI and meeting the criteria for PTSD will be included in the study. Participants will be randomized after baseline assessment to either treatment as usual plus waiting list for EMDR or to treatment as usual plus EMDR. The EMDR condition comprises nine sessions, around 60 min in length delivered weekly, the first of which is a case conceptualization session. The primary outcomes are clinician and participant-rated symptoms of PTSD, and adverse events. Secondary outcomes include psychotic symptoms, social functioning, level of disability, self-esteem, depressive symptoms, post-trauma cognitions, and broad domains of complex posttraumatic difficulties. A trained assessor blinded to the treatment condition will assess outcomes at baseline, 10 weeks, and 6 months. Additionally, grounded theory qualitative methods will be used to explore participant experience of EMDR for a subset of participants.

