#### Primary outcome measurements: PTSD symptoms, adverse events, and treatment acceptability

There are two primary outcome measures pertaining to PTSD symptoms, two regarding treatment safety, and one measure of the acceptability of EMDR treatment. The first primary outcome measure is the CAPS, which is a 30-item structured interview that assesses DSM-5 PTSD symptoms [37]. The CAPS will be used to assess the presence or absence of PTSD diagnosis and the frequency and intensity of the clinician-rated PTSD symptoms.

**Table 1 Tab1:** Secondary outcome measures

Secondary outcome	Measurement instrument^a^	T0	T1	T2
Posttraumatic cognitions	PTCI (s)	X	X	X
Self-disturbance	TSI-2 Factor 1 (s)	X	X	X
Posttraumatic stress	TSI-2 Factor 2 (s)	X	X	X
Externalization	TSI-2 Factor 3 (s)	X	X	X
Somatization	TSI-2 Factor 4 (s)	X	X	X
Depression	BDI-II (s)	X	X	X
Psychosis	PSYRATS (i)	X	X	X
Overall functioning	WHODAS 2.0 (i)	X	X	X
Social functioning	Social Functioning Scale (i)	X	X	X
Self-esteem	RSES (s)	X	X	X

^a^ (i) = measurement interview, (s) = self-report

BDI-II, Beck Depression Inventory—second edition; PTCI, Posttraumatic Cognitions Inventory; PSYRATS, Psychotic Symptom Rating Scales; RSES, Rosenberg Self-Esteem Scale; T0, baseline; T1, post treatment; T2, 6-month follow-up; TSI-2, Trauma Symptom Inventory—second edition; WHODAS, World Health Organization Disability Assessment Scale

**Table 2 Tab2:** Items from the World Health Organization Trial Registration Data Set

Data category	Information
Primary registry and trial identifying number	Australia and New Zealand Clinical Trials Network, registration number ACTRN12618000683235 (registered prospectively)
Date of registration in primary registry	26 April 2018
Sponsor	University of Otago Contact details: Office of Research and Enterprise, Otago University, [name]. Tel. [name]
Contact for public/scientific queries	[contact]
Public title	Eye movement desensitization and reprocessing (EMDR) therapy for posttraumatic stress disorder in adults with serious mental illness within forensic and rehabilitation services: a study protocol for a randomized controlled trial
Scientific title	Eye movement desensitization and reprocessing (EMDR) therapy for posttraumatic stress disorder in adults with serious mental illness within forensic and rehabilitation services: a study protocol for a randomized controlled trial
Countries of recruitment	New Zealand

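### The planned PSYRATS tests either cannot compare the arms or cannot adjust for the baseline score that the trial collects; one baseline-adjusted between-arm analysis would be better

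*Protocol article*

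**What the plan says.** The Quantitative data analysis section gives the general rule "Continuous variables will be analyzed on an intention-to-treat basis with linear mixed models". It then makes an exception for PSYRATS, whose scores are "usually not normally distributed because of a disproportionate number of zero scores", and states that "differences will be analyzed using the Wilcoxon signed-rank test", with the Mann–Whitney U test named beside it. The next paragraph specifies "Baseline scores will be included as covariates, time as a categorical variable, and treatment condition as a fixed effect", with a random intercept.

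The row for this outcome in Table 1 reads "Psychosis PSYRATS (i) X X X", the three marks standing for T0, T1 and T2. The abstract places psychosis among the secondary outcomes: "Secondary outcomes include psychotic symptoms, social functioning, level of disability, self-esteem, depressive symptoms, post-trauma cognitions". The Secondary aims section frames the question as the effect of EMDR against the waiting list.

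The article does not say which of the two rank tests carries the treatment conclusion, or whether Mann–Whitney is applied to follow-up scores or to change from T0.

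**The concern.** Neither named test does for PSYRATS what the mixed model does for the other continuous outcomes.

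- **Signed-rank test.** It needs paired observations, and the randomised arms are independent. It can only assess change over time, within an arm or pooled, which is not the question in the Secondary aims.
- **Mann–Whitney test.** It compares the arms but has no place for a covariate. The baseline-covariate sentence cannot rescue it, because that sentence goes on to categorical time and a random intercept and so describes the mixed model.

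The reason given for the exception does not require the loss of adjustment. Rank ANCOVA and ordinal models accommodate zeros and ties.

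This matters for a practical reason. The AEQ items that the article lists include no psychotic symptoms. The session rating scale asks about hearing voices, but it is given around treatment sessions, which waiting-list participants do not have before T2. PSYRATS is therefore the only listed psychosis scale that allows a randomised comparison. With 46 participants and non-stratified randomisation, chance imbalance at T0 is plausible and would be left uncorrected under Mann–Whitney on follow-up scores.

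**Working it through.** **Figures in the plan.** The article gives no power or sample size for PSYRATS. Its figures concern CAPS: difference 16, SD 16, two-sided 0.05, power 0.80, 15 per arm, and 23 per arm after 30% dropout. The normal approximation gives 2 × (1.96 + 0.84)² × (16/16)² = 15.7, so 16 per arm, close to the stated 15. Then 16/0.7 = 22.9, which rounds up to the stated 23. For PSYRATS the useful figure is the evaluable number: 23 × 0.7 = 16.1, or about 16 per arm.

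**Normal-theory check.** Power = Φ(d√(n/2)/k − 1.96), with k = 1 unadjusted and k = √(1 − r²) for ANCOVA. With d = 0.8 and n = 16, d√(n/2) = 2.263.

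- Unadjusted: Φ(2.263 − 1.96) = 0.62
- ANCOVA, r = 0.5: Φ(2.263/0.866 − 1.96) = 0.74
- ANCOVA, r = 0.7: Φ(2.263/0.714 − 1.96) = 0.89

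**Simulation with excess zeros.** Latent normal scores at baseline and follow-up have correlation ρ. Values below a threshold are set to zero, and values above it are scaled and rounded to integers. Rank ANCOVA regresses follow-up ranks on baseline ranks and arm. The zero share, correlation and effect are assumptions; the documents give none of them. Power in % at 16 per arm, 0.8 SD effect, 2,500 trials per row:

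| Zeros | ρ | Mann–Whitney, follow-up | Mann–Whitney, change | Rank ANCOVA | Gain over follow-up |
|---|---|---|---|---|---|
| 30% | 0.5 | 51.4 | 41.2 | 60.3 | 8.9 |
| 30% | 0.7 | 50.2 | 56.8 | 70.9 | 20.7 |
| 30% | 0.85 | 51.4 | 78.7 | 86.6 | 35.2 |
| 50% | 0.5 | 43.4 | 29.0 | 48.8 | 5.4 |
| 50% | 0.7 | 43.4 | 38.4 | 58.2 | 14.8 |
| 50% | 0.85 | 42.4 | 54.0 | 71.5 | 29.1 |

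With all 23 per arm evaluable, the gain over follow-up scores runs from 64.0 − 58.6 = 5.4 points to 96.7 − 67.0 = 29.7 points.

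**Less favourable settings.** Quade rank ANCOVA, 16 per arm, 2,000 trials per cell, power in %:

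| Effect | Zeros | Mann–Whitney, ρ = 0.6 / 0.8 | Quade, ρ = 0.6 / 0.8 | Gain |
|---|---|---|---|---|
| 0.8 SD | 70% | 30 / 31 | 35 / 43 | 5 / 12 |
| 0.4 SD | 30% | 16 / 18 | 22 / 33 | 6 / 15 |
| 0.4 SD | 50% | 14 / 15 | 18 / 26 | 4 / 11 |
| 0.4 SD | 70% | 11 / 13 | 13 / 18 | 2 / 5 |

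The smallest gain comes from rounded values (11 and 13), so it lies between 1 and 3 points. The Monte Carlo standard error of one such power is about √(0.12 × 0.88/2000) = 0.7 points.

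**Type I error.** With no arm difference, the rejection rate in the main simulation was 0.036–0.058 across both Mann–Whitney variants and 0.040–0.055 for rank ANCOVA.

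**Reading signed-rank results arm against arm.** If both arms truly change alike and each test has power p, exactly one is significant with probability 2p(1 − p), at most 50%. In the simulation, a common 0.4 SD improvement with no arm difference gave this pattern in 34–51% of trials at 16 per arm. With no change at all it occurred in 8–10% (16 or 23 per arm).

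**The case against.** The strongest case on the other side has four parts.

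- **The plan already contains a valid comparison.** Mann–Whitney is a direct randomised comparison that holds its error rate. This stands: its fault is inefficiency. A reader might infer that the trial will claim an effect because one arm is significant and the other is not. The article nowhere says so; the 34–51% describes a possible misuse that the wording leaves open.
- **Safety is not at issue.** A reader might take PSYRATS as the trial's main test of psychosis safety. The article lists it as one of 10 secondary outcomes on psychopathology and assigns safety to the AEQ and the session rating scale. That stands too, although neither of those gives a randomised comparison of psychotic symptoms from the items described.
- **Differences may mean change scores, which use T0.** That reading is open, and such detail may sit in an analysis plan that is not shown. But the choice of tests is stated, and in all six settings tabulated, change scores had less power than rank ANCOVA. In three of them they also had less than follow-up scores.
- **The gain may be small.** Eligibility needs only a lifetime psychotic disorder and excludes acute psychosis, so zeros could be frequent and effects modest. In the less favourable settings, neither test has adequate power. This limits the size of the point, not its direction.

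**Conclusion.** The point holds as a modest improvement to one secondary outcome. The signed-rank test cannot answer the treatment question. The Mann–Whitney test answers it validly but without the baseline adjustment used for the other continuous outcomes, and the stated reason (zeros) does not justify that loss.

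At 16 evaluable per arm, baseline adjustment adds roughly 1 to 35 points of power over Mann–Whitney on follow-up scores. It was better in every setting examined; the comparison with change scores was made only at 0.8 SD. The range rests on assumed values: 30–70% zeros, latent correlation 0.5–0.85 and effects of 0.4–0.8 SD. The upper end needs a high correlation and a large effect. The proportional-odds option in the fix was not simulated.

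**What to change.** State that the PSYRATS treatment comparison at T1 and at T2 is a single between-arm analysis adjusted for T0, using one of the following:

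- a proportional-odds model with the T0 score as covariate, reporting the odds ratio and confidence interval; or
- Quade rank ANCOVA with an effect measure adjusted in the same way, such as the adjusted difference in mean ranks.

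An unadjusted Hodges–Lehmann shift should not accompany the Quade test. It ignores baseline and collapses under ties: in simulation with a true 0.8 SD effect it was exactly zero in about 63% of trials at 50% zeros and 96% at 70%. It could therefore report no difference beside a significant test.

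Label signed-rank results as descriptive only. The cost is a change of wording and minor analysis work; T0 PSYRATS is already scheduled, so no new data, visits or participants are needed.

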Secondly, the Posttraumatic Stress Disorder Symptom Scale—Self-Report (PSS-SR) [38] will be administered to assess self-reported severity of PTSD symptoms [39]. The PSS-SR consists of 17 items corresponding to the 17 diagnostic DSM-IV-TR criteria of PTSD which are rated on a 3-point Likert scale, where 0 = *not at all*, 1 = *a little* bit, 2 = *somewhat*, and 3 = *very much*. This yields a total score measuring symptom severity (range 0–51), as well as separate severity scores for re-experiencing (range 0–15), avoidance (range 0–21), and arousal (range 0–15). The PSS-SR will also be administered at T0, T1, and T2, as well as before each treatment session, to assess changes in the PTSD symptoms during treatment. The PSS-SR has revealed satisfactory internal consistency (Cronbach’s α = 0.91), high test–retest reliability (*r* = 0.74), and good concurrent validity (sensitivity = 62%, positive predictive power = 100%, negative predictive power = 82% [38, 40]).

Two primary outcome measures pertain to adverse events. The Adverse Events Questionnaire (AEQ), which we have designed using similar questions to Van den Berg et al. [16], is a checklist that will help establish treatment safety. In 10 questions, the patient is asked to report any experiences they have had over the last 2 months of self-harm, suicide attempt, deliberately hurting another person, excessive use of alcohol, excessive use of drugs, having needed help because of a crisis, moving back to a higher level of security within the services, or any reoffending.

The Adverse Events Session Rating scale will also be used to assess adverse events in the participant before and after treatment sessions (sessions two and three), for example, being suicidal and hearing voices. Participants will respond on a 10-point visual analog scale (from “*no, not at all*” to “*yes, very much*”) to the questions.

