### Trial monitoring and oversight

The risks of the study are thought to be low based on previous research, which has found EMDR to be safe, effective, and well tolerated in people with serious mental illness. However, the population is vulnerable so there are a number of safeguards in place. A Data Monitoring Committee (DMC) has been set up as an advisory body responsible for monitoring emerging safety and efficacy data, reviewing trial conduct and making recommendations. The DMC is independent of the study organizers and funders. Its membership is multidisciplinary and comprises the Clinical Director (Chair) and Operations Manager from the Central Regional Forensic and Rehabilitation Service, a senior psychologist not related to the study, and the principal investigator. During the recruitment period, interim analyses will be supplied in strict confidence to the DMC, together with any analyses the DMC may request.

The base rate of serious events in this population is much higher than in the general population, and it may be difficult to establish whether such events are related or unrelated to therapy. All serious adverse outcomes will be reported immediately to the DMC. We have predetermined that any serious event such as a serious deliberate self-harm attempt (requiring medical attention), an assault on another person (requiring medical attention), or a return to an environment of high security will be a reason for the participant being withdrawn from the study. Any other significant adverse effects will be discussed on a case-by-case basis. The DMC and research team will formally review the feasibility and safety of the study after data have been collected on 10 participants, before further participants are recruited.

The terms of reference of the DMC are available on request from the principal investigator.

In the unlikely event that someone is harmed in the course of the trial, they would be eligible under New Zealand law to apply for compensation from the Accident Compensation Corporation. This is explained in the informed consent process.

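### Logistic GEE, fixed for every dichotomous outcome, gives no valid bound on harm for uncommon adverse-event items when an arm has no events

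*Protocol article*

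**What the plan says.** The Quantitative data analysis section of the protocol article gives one rule for binary data, namely "logistic generalized estimating equation analyses with exchangeable correlation structure". It continues: "Effects will be calculated for post treatment and 6-month follow-up using interaction effects". The model therefore has a separate arm contrast at each of the two visits. The section makes an exception for the PSYRATS, which goes to rank tests because many participants score zero. It makes no such exception for binary outcomes.

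The section on primary outcome measurements states: "Two primary outcome measures pertain to adverse events". One is the AEQ, which "is a checklist that will help establish treatment safety". Its format is: "In 10 questions, the patient is asked to report any experiences they have had over the last 2 months". The items range from suicide attempt and reoffending to alcohol use and needing help in a crisis. The other is a session rating: "Participants will respond on a 10-point visual analog scale".

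The analysis section does not name adverse events, and the AEQ's scoring (item by item, any event, or a count) is not given. No event rate is stated. The section on trial monitoring says only: "The base rate of serious events in this population is much higher than in the general population".

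**The concern.** An arm-by-visit logistic model reproduces the log odds in each of its four cells. If a cell has no events, its log odds go to minus infinity and the odds ratio for that visit does not exist. Software stops at an arbitrary large number. The sandwich standard error, which is built from residuals, is then meaningless: the residuals in an empty cell are practically zero, so the cell adds almost nothing to the estimated variance.

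Safety is a primary aim, and the AEQ is the measure that can compare such events between arms. The session rating is taken around EMDR sessions, which the waiting list does not have before T2. The method fails in the most reassuring case, no events on EMDR, when readers most need to know how large a harm remains compatible with the data. It can also fail silently, printing an extreme p-value in place of an error.

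**Working it through.** **Inputs.** From Sample size calculations: 23 recruited per arm and 30% dropout. From Quantitative data analysis: logistic GEE, exchangeable, arm by visit. Assumed, because no figure is given: the event rate p per arm and visit, equal in both arms.

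**The plan's own figures.** For a difference of 16 and an SD of 16, the normal approximation gives 2 × (1.96 + 0.84)² = 15.7, so 16 per arm against the stated 15. Then 16 / 0.7 = 22.9, so 23, the stated recruitment target. After dropout 23 × 0.7 = 16.1 remain. The range here is therefore 16 to 23 per arm.

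**Chance of an empty arm at one visit.** One arm is empty with probability q = (1 − p)^n, and at least one of two with probability 1 − (1 − q)². For p = 10% and n = 23, q = 0.9^23 = 0.089 and 1 − 0.911² = 0.17.

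| Assumed rate | n = 16: one arm / either arm | n = 23: one arm / either arm |
|---|---|---|
| 2% | 0.72 / 0.92 | 0.63 / 0.86 |
| 5% | 0.44 / 0.69 | 0.31 / 0.52 |
| 10% | 0.19 / 0.34 | 0.09 / 0.17 |
| 20% | 0.03 / 0.06 | 0.01 / 0.01 |
| 30% | 0.003 / 0.007 | 0.000 / 0.001 |

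**Chance that any of the four arm-by-visit cells is empty** (simulation, within-person correlation 0.3 assumed), n = 23 to n = 16: 73% to 86% at a 5% rate, 29% to 53% at 10%, 3% to 11% at 20%.

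**What the model prints.** The GEE was fitted to small example tables (T1 and T2 counts, one arm against the other):

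- 0/16 and 1/16 against 3/16 and 2/16: log odds ratio at T1 about 31, SE about 630,000.
- 0/16 and 0/16 against 3/16 and 2/16: log odds ratio at T1 about −24.1, SE 0.69, so z is about −35 and p about 4 × 10^-269. With the other arm as reference the SE is 0.64 and z = 24.1 / 0.64 = 37.7. The same data give a different test statistic, which shows that the number is an artefact.
- No empty cell (4/23 and 3/23 against 2/23 and 2/23): log odds ratio −0.79, SE 0.92. The method works.

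**What a direct method gives for 0/16 against 3/16.** Fisher's exact p = 0.23. The risk difference is 0 − 0.1875 = −0.1875. The Wilson limits are 0 to 0.194 and 0.066 to 0.430. Newcombe lower limit: −0.1875 − √(0² + 0.2426²) = −0.430. Upper limit: −0.1875 + √(0.1936² + 0.1216²) = +0.041. The data thus remain compatible with up to about 4 points more events in the empty arm. For a single arm the exact two-sided 95% upper limit is 1 − 0.025^(1/16) = 21% for 0/16 and 1 − 0.025^(1/23) = 15% for 0/23.

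**The case against.** The strongest reply is that the article never says it will run GEE on adverse events. The analysis section names only loss of diagnosis and remission as binary results, one of the two safety measures is a visual analog scale, and the AEQ might be scored as a composite or a count. Event rates may also be high. The article says that serious events are more frequent here than in the general population, and some items concern common behaviours. The 16 per arm is the planned worst case: with 15% dropout about 20 remain, and at a 10% rate the chance of an empty arm is about 23% per visit, not 34%. Descriptive summaries and the monitoring committee's review do not depend on an odds ratio. A sparse-data fallback is often left to the analysis plan.

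Most of this limits the point and is accepted. It does not remove it. A yes/no item is dichotomous, and the article gives no other method for such data. The problem is also more than a missing fallback: the stated rule, followed as written, can return a wrong p-value without warning.

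A reader might go further in four ways that the documents do not support:

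- That the primary safety analysis as a whole has no usable result. This would require item-level analysis of uncommon events, which is not stated.
- That failure on at least one of ten AEQ questions is near certain. This assumes ten separate models and rates that nobody has given.
- That loss of diagnosis is affected. No sparsity is shown for it, and at an assumed 40% rate a simulation of the GEE gave a type I error of 4% to 6%.
- That the number needed to treat is undermined. It is planned for loss of diagnosis or remission and can be taken from the two raw proportions.

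**Conclusion.** The point holds in a conditional form and is minor. For AEQ items with rates of 5% to 10% per arm and visit, at least one arm is empty at a given visit in about 17% (10%, n = 23) to 69% (5%, n = 16) of trials, and more often for rarer items. The specified GEE then gives neither a valid estimate nor a valid bound on harm. For an any-event composite at 20% the figure is about 1% to 6%, so such an analysis would rarely be affected.

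This rests on two things that the article does not settle: that AEQ items are analysed as binary outcomes, and the event rates, which are assumptions with equal rates in both arms. The failure of the model in an empty cell rests on neither.

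**What to change.** State how the AEQ is scored. For AEQ items and any other sparse adverse-event outcome, make the primary analysis the between-arm risk difference at T1 and, separately, at T2, with a Newcombe or exact unconditional confidence interval. Apply it whatever the observed counts, so that the method is not chosen after an empty cell has been seen. If an odds ratio is also wanted, use Firth-penalised logistic regression at each visit. Keep GEE for loss of diagnosis.

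The cost is a few sentences of analysis wording; sample size, visits and data collection stay as they are. The intervals are slightly conservative, and T1 and T2 are not pooled, so any gain from the repeated measure is given up for these outcomes.

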### Sample size calculations

The power is based on information from investigations in related, but not identical, clinical groups to those planned to participate in this trial.

In an RCT investigating EMDR in mental health outpatients with psychosis and PTSD [24], the post-treatment CAPS score for EMDR was 40.3 (*n* = 55), compared with 56.5 (*n* = 47) for the waiting list, a difference of 16 points. The baseline mean (SD) CAPS score for these trial participants was 69.9 (16.2).

A 15-point change in CAPS total severity score has been proposed as a marker of clinically significant change [32], and so we feel that a difference of 16 points on the CAPS is clinically significant, and is likely to represent the difference between severe and moderate symptoms, or moderate and mild (subthreshold) symptoms.

Fifteen participants per arm are needed to detect a change of 16 points with an SD of 16 points using a *t* test and based on equal proportions of participants randomized to each group with a two-sided type I error rate of 0.05 and power of 0.8.

We estimate that attrition could be as much as 30%, although this is likely to be a conservative estimate as a meta-analysis reports that the dropout rate for trauma-focused interventions is around 18% and our previous research in this forensic patient group [29, 54, 55] has found participants to be well engaged with low dropout rates (< 15%). A conservative estimate of dropout is reasonable because the studies in the meta-analysis were over shorter timeframes, and we anticipate that some participants may have been discharged, changed address, or otherwise been lost to follow up at the 6-month mark. Based on the 30% dropout rate, the trial would need to recruit 23 participants per arm.

An important consideration is that we are uncertain whether the SD of the outcome variable will be as previously reported. To this end, we will initially plan to recruit 2 × 8 participants in order to estimate the SD, as the number of participants gives reasonable precision for this estimation. This will also enable us to determine preliminary efficacy, safety, and acceptability data, before further recruiting takes place.

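### The last-observation-carried-forward robustness analysis makes no exception for the Adverse Events Questionnaire, so a missing T1 form would be filled with answers about the time before randomisation

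*Protocol article*

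**What the plan says.** The Quantitative data analysis section of the protocol article sets out these rules:

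- Main model for binary outcomes: "Dichotomous outcomes will be analyzed with logistic generalized estimating equation analyses with exchangeable correlation structure".
- Missing data in general: "We will use multiple imputations for missing data".
- Robustness: an analysis of completers and "intent-to-treat analyses with the last observation carried forward (with missing data on loss of diagnosis conservatively replaced with a negative value"). These "will be performed to test the robustness of the findings". No outcome other than loss of diagnosis has its own rule.

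On the measure itself, the primary outcome section states: "There are two primary outcome measures pertaining to PTSD symptoms, two regarding treatment safety". The AEQ is one of the safety measures, and in it "the patient is asked to report any experiences they have had over the last 2 months of self-harm, suicide attempt" and other events. The Outcome measures section places the primary, secondary and tertiary measures at T0, T1 (10 weeks) and T2 (6 months). The randomisation section puts T0 before allocation.

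On serious events, Trial monitoring and oversight states: "All serious adverse outcomes will be reported immediately to the DMC". The same section makes self-harm or assault needing medical care, or a move back to high security, grounds for taking the participant out of the study.

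On loss to follow-up, the sample size section states: "We estimate that attrition could be as much as 30" per cent.

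**The concern.** Carrying a value forward assumes that the last recorded state still describes the participant at the missed visit. A symptom score can be argued over on those terms. A look-back checklist of events cannot, because each form reports on its own window. The T0 window closes before randomisation, so a T0 answer says nothing about harm during the trial.

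Two things are at stake:

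- A pre-trial event, or its absence, is counted as an on-trial result. When loss is unrelated to events, this pulls any difference in harm between the arms towards zero, whichever arm has more. If EMDR truly caused more events, the check would understate the excess, and a safety conclusion called robust would owe part of that to the fill-in rule.
- The events that lead to withdrawal overlap with AEQ items (self-harm, hurting another person, moving to higher security). The event itself can remove the form that should record it. The plan gives loss of diagnosis a deliberately cautious rule when it is missing, but harm gets none.

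**Working it through.** **Which missing visits cause the problem.** Two months is 2 × 365.25/12/7 = 8.7 weeks.

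- T1 missing, T2 seen: T1 is filled from T0, which is before randomisation.
- T1 and T2 both missing: both are filled from T0.
- T1 seen, T2 missing: T2 is filled from T1. With T1 at 10 weeks, its window opens about 10 − 8.7 = 1.3 weeks into the trial, so the value is on-trial but from an earlier period. If T1 is at 2 months, as the Recruitment section has it, the window still opens at about the start of treatment.

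Pre-randomisation answers therefore enter only when T1 is missing.

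**How many participants.** The plan recruits 23 per arm and allows for 30% attrition. That is 23 × 0.30 = 6.9, about 7 per arm or 14 of 46, and leaves 23 × 0.70 = 16.1 per arm against the 15 required. The article gives no figure for AEQ loss. It justifies 30% partly by losses at 6 months, and cites about 18% in a meta-analysis and under 15% in its own earlier studies. So 30% is an upper bound at T1.

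**Loss unrelated to events.** Let p be the true T1 event rate in an arm, b the T0 rate (equal across arms by randomisation) and m the share with T1 missing (the same in both arms).

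Carried-forward rate = (1 − m)p + mb, so risk difference = (1 − m)(p_EMDR − p_WL).

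The document gives no event rates. Assume 40% in EMDR and 20% on the waiting list:

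| m | Risk difference |
|---|---|
| 0.15 | 0.85 × 20 = 17.0 points |
| 0.18 | 0.82 × 20 = 16.4 points |
| 0.30 | 0.70 × 20 = 14.0 points |

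For example, with m = 0.30 and b = 0.30, the rates are 0.28 + 0.09 = 0.37 and 0.14 + 0.09 = 0.23, a difference of 0.14.

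**Loss related to events.** Keep 40% and 20% and overall loss at 30%, and assume 60% of those with an event are lost. Observed events are 0.40 × 0.40 = 0.16 and 0.20 × 0.40 = 0.08.

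- Observed cases only: 0.16/0.70 − 0.08/0.70 = 0.114.
- Carried forward, T0 history unrelated to on-trial events: (0.16 + 0.30b) − (0.08 + 0.30b) = 0.08.
- Carried forward, T0 rate 30%, and T0 history raising on-trial risk to 80% and 40%. Lost participants with a T0 event in EMDR: 0.30 × 0.80 × 0.60 = 0.144 with an event, plus 0.06 × 0.10 = 0.006 without, giving 0.150. On the waiting list: 0.30 × 0.40 × 0.60 = 0.072, plus 0.18 × 0.225 = 0.0405, giving 0.1125. Risk difference = 0.31 − 0.1925 = 0.1175.

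The answer moves from 8 to 11.75 points on one untested assumption.

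**Withdrawal caused by the event.** Suppose 4 EMDR and 1 waiting-list participants are withdrawn for a serious event before T1, and 10% to 50% of participants reported an event at T0 (all assumed). Carrying forward would count on average 4 × 0.10 to 4 × 0.50 = 0.4 to 2.0 of the 4, and 0.1 to 0.5 of the 1.

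**The case against.** The case on the other side has real force.

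- **It is only a robustness run.** The main analysis is the logistic model, with multiple imputation as the general method for missing data. That stands: a reader might infer that carrying forward governs the safety result, and the document does not say so.
- **The AEQ is not named in the rule.** The sentence sits among effect estimates and its parenthesis concerns diagnosis, so efficacy may have been meant. The AEQ's T0 form also rests on the general schedule statement, which cannot be literal for every measure because the session rating scale is tied to particular sessions. Both points stand as caveats. Even so, this is more than missing detail: a general rule with one listed exception is stated, and it does not suit a primary outcome.
- **Serious events may well be used.** A reader might infer that events reported to the monitoring committee are left out of the safety analysis. Nothing says that. The document is silent, and an analysis plan not shown may cover it. What can be said is that the missing-data rules as stated make no provision for them.
- **Follow-up continues.** Those who stop treatment are to be assessed at T1 and T2 where possible. This reduces the problem but does not remove it, because the monitoring section speaks of withdrawal from the study.
- **The shift is small against the noise.** At 40% and 20% with 23 per arm, the standard error is √(0.24/23 + 0.16/23) = 0.13, a 95% interval of about ±26 points. A shift of 3 to 6 points would not decide the trial. That stands, but it does not justify using the wrong period's data when a better source exists.

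**Conclusion.** The point holds in a limited form. Read literally, the carried-forward robustness analysis would fill a missing T1 AEQ with answers about the time before randomisation, and the stated missing-data rules do not say how an event that caused the withdrawal is counted.

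With T1 loss unrelated to events and equal across arms, the dilution equals the missing share: an assumed 20-point difference becomes about 17 points at 15% loss and 14 at 30%, the upper bound.

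With event-related loss, no single figure is defensible. It is tempting to say that the risk difference is then free of the T0 rate and falls to 8 points. That needs T0 history to be unrelated to on-trial events. Randomisation balances T0 answers among all those randomised, not among those who drop out because of an event.

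It would also be too wide to say that missing either T1 or T2 brings in pre-trial events; T1 must be missing. All event rates used here are assumptions.

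**What to change.** In the Quantitative data analysis section:

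1. Exempt the AEQ from the carried-forward analysis, so that a T0 form is never used for T1 or T2.
2. State that when an AEQ is missing, items covered by serious-event reporting (serious self-harm, serious assault, return to high security) are scored from the reports already made to the monitoring committee, with the source tabulated by arm.
3. Keep the stated multiple imputation for the remaining items. A worst-case sensitivity analysis may be added but is optional.

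The cost is a few sentences and linking existing reports to the AEQ data, with no new assessment. The small downside is that serious items then come from two sources, self-report and staff report, which is why the source should be shown by arm.
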